### **3.4 Follow-up Plan**

On the day before the parturient's surgery (T0), researchers will collect baseline data, and assess sleep at T0 on the morning of the surgery. On the day of the surgery, before the first intervention (T1), blinded researchers will evaluate the peak uterine contraction pain and incision pain. After the first intervention (T2), depression and anxiety will be assessed, followed by re-evaluation of peak uterine contraction pain and incision pain during this period. Sleep at T2 will be assessed on the morning of the first postoperative day. Before the second intervention (T3), peak uterine contraction pain and incision pain will be evaluated. After the second intervention (T4), depression, anxiety, postpartum recovery quality, and peak uterine contraction pain and incision pain during this period will be assessed. Sleep at T4 will be evaluated on the morning of the second postoperative day. Before the third intervention

(T5), peak uterine contraction pain and incision pain will be evaluated. After the third intervention (T6), depression, anxiety, postpartum recovery quality, and peak uterine contraction pain and incision pain during this period will be assessed. On the morning of the third postoperative day (T7), sleep at T6 will be evaluated, along with peak uterine contraction pain, incision pain, depression, anxiety, and postpartum recovery quality. At 1 month postpartum (T8), the telephone follow-up will assess the parturient's depressive and anxiety status.

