#### **3.5.2 Secondary outcomes**

1) Peak uterine contraction pain scores during the three days postoperatively (assessed by the VAS). The contraction pain scores are measured before the

first intervention (T1), after the first intervention (T2), before the second intervention (T3), after the second intervention (T4), before the third intervention (T5), after the third intervention (T6), and the third postoperative day (T7).

2) Incision pain scores at T1-T7 (assessed by the VAS).

3) Maternal anxiety scores at T2, T4, T6, T7 and the first month postpartum [T8] (assessed by the Pregnancy-Related Anxiety Questionnaire-Revised 2 [PRAQ-R2], comprising 10 items, each rated on a 5-point scale [1-5], with higher scores indicative of increased pregnancy-related anxiety).

4) Maternal depression scores at T2, T4, T6, T7, and T8 (assessed by the Edinburgh Postnatal Depression Scale [EPDS], including 10 items, scored on a 4-point scale [0-3], with higher scores denote more severe depressive symptoms).

5) Sleep quality at T2, T4 and T6 (assessed by the Leeds Sleep Evaluation Questionnaire [LSEQ], with higher scores indicating better sleep quality).

6) Quality of postpartum recovery at T4, T6 and T7 (assessed by the 11-item Obstetric Quality Recovery Scale [ObsQoR-11], with a total score range of 0-110).

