### **3.6 Statistical Analysis**

Descriptive statistics will include the Chi-squared test or Fisher exact test for categorical variables expressed as frequency. Assessment for normal distribution will be performed with the Shapiro–Wilk test. Normally distributed data will be presented as mean and standard deviation (SD) and compared by the independent sample t-test. Non-normally distributed data will be presented as median and interquartile range (IQR) and compared by the Mann-Whitney U test.

For data collected at multiple time points, we will adopt the Generalized Estimating Equations (GEE). First, we will test the interaction between treatment and time. If this interaction is significant, we will test the between-group differences at each time point and use the Bonferroni test to adjust for multiple comparisons. Otherwise, we will next test the main effect of treatment, and the Bonferroni correction will not be performed for the treatment effects at each time point. For the comparison of the incidence rate of moderate to severe postpartum contraction pain, the GEE model will include the following settings: covariates: intervention group, time, intervention  $\times$  time interaction; link function: logit function; group variable: participant; intraclass

correlation structure: independent. The GEE models for contraction pain score, incision pain score, depression score, anxiety score, sleep score, and recovery quality score will include the following settings: covariates: intervention group, time, intervention  $\times$  time interaction; link function: identity link; group variable: participant; intraclass correlation structure: independent. Data will be analyzed using SPSS version 27.0 (IBM Corp., Chicago, ILUSA) and GraphPad Prism V.9 (GraphPad Software, San Diego, CAUSA), with  $P < .05$  considered statistically significant.

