### **3.8 Intervention with taVNS**

On the day of delivery, the first postpartum day, and the second postpartum day, the intervention group received three sessions of active taVNS in total, and the control group received three sessions of sham taVNS in total. Electrical stimulation is applied through electrodes placed on the left concha of the ear (tVNS501; Changzhou Ruishen'an Medical Devices Co., Ltd.). In the active taVNS group, participants receive taVNS (pulse width: 200  $\mu$ s; frequency: 20 Hz) for 30 minutes, with the current increasing for 30 seconds until the participant reports a tingling sensation, then decreasing to a level slightly below this threshold for 30 minutes. In the sham taVNS group, electrodes are positioned similarly, with the current increasing for 30 seconds until the participant reported a tingling sensation, then decreasing to a level slightly below this threshold, after which the device remained off for the following 30 minutes to simulate the sham state. Throughout the intervention, researchers closely monitor participants for any adverse effects and stop the

stimulation immediately if intolerable side effects are observed.

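### The pooled treatment effect on the secondary pain scores mixes ratings made just after a session with ratings made before the next session or on day 3, and so estimates neither acute nor carry-over relief

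*Protocol*

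**What the plan says.** Section 3.4 of the protocol schedules uterine contraction pain and incision pain at seven points. After the first session the instruction is a "followed by re-evaluation of peak uterine contraction pain and incision pain during this period"; the same qualifier appears after the second and third sessions (T4, T6). The other ratings carry no qualifier: "Before the second intervention (T3), peak uterine contraction pain and incision pain will be evaluated", likewise before the third session (T5), and finally "On the morning of the third postoperative day (T7), sleep at T6 will be evaluated, along with peak uterine contraction pain". The period meant at T2, T4 and T6 is not defined, and no recall window is given for T1, T3, T5 or T7.

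Section 3.8 gives one session on each of three days, "On the day of delivery, the first postpartum day, and the second postpartum day", each lasting 30 minutes. T3, T5 and T7 therefore fall on the day after the preceding session.

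Section 3.5.2 combines the seven contraction-pain ratings into one secondary outcome, "Peak uterine contraction pain scores during the three days postoperatively (assessed by the VAS)", and names the visits one by one: "first intervention (T1), after the first intervention (T2), before the second intervention (T3), after the second intervention (T4), before the third" session, and so on to T7. Incision pain is also listed at T1-T7.

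Section 3.6 fits a GEE with group, time and their interaction under an independent working correlation. The interaction is tested first. If it is significant, groups are compared at each time point with a Bonferroni adjustment. "Otherwise, we will next test the main effect of treatment", without Bonferroni correction for the effects at each time point.

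**The concern.** A main effect over visits is easy to interpret when every visit measures the same thing. Here alternate ratings appear to measure two things: pain around stimulation, and pain after the stimulation has been off until the next day. The protocol's background section describes this pain as intermittent, and the peak of an intermittent pain also depends on how long a window it is taken over.

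Acting during a session and acting between sessions are separate clinical claims. If taVNS does only one of them, the average over both sets understates that effect and may miss it. If the average is positive, it cannot show which claim is supported, yet the outcome's title invites reading it as three-day relief. Keeping pre-treatment T1 as an outcome level dilutes the average further, because no treatment effect is possible there.

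**Working it through.** **Inputs from the protocol.** Seven pain visits: T1 before treatment, three after sessions (T2, T4, T6), and three before the next session or on day 3 (T3, T5, T7). Independent working correlation, so visits are weighted equally when data are complete. 70 evaluable women per group (section 3.7).

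**Sample size.** The protocol gives no figure on the present point, so only the n is checked. n = (1.960 + 0.842)² × (0.35×0.65 + 0.15×0.85) / 0.20² = 69.66, rounded up to 70; 70/0.90 = 77.8, rounded up to 78. Both stated figures reproduce.

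**Assumed inputs.** SD 2 on a 0-10 scale, equal correlation ρ between visits of 0.3, 0.5 or 0.7, complete data.

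**Step 1: dilution.** Let an effect D exist in one phase only.
- Average over T1-T7: 3D/7 = 0.43D.
- Average over T2-T7: 3D/6 = 0.50D.
- Effect in both phases, T1 kept as an outcome: 6D/7 = 0.86D.

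**Step 2: how often the interaction test misses a one-phase effect.** Simulation of 2,000 trials per cell, Wald test at 5%; share of trials with a non-significant interaction:

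| D | Visits | ρ = 0.3 | ρ = 0.5 | ρ = 0.7 |
|---|---|---|---|---|
| 0.5 | T1-T7 | 60% | 47% | 21% |
| 0.5 | T2-T7 | 65% | 51% | 25% |
| 0.75 | T1-T7 | 24% | 11% | 1% |
| 0.75 | T2-T7 | 29% | 15% | 2% |
| 1.0 | T1-T7 | 4% | 1% | 0% |
| 1.0 | T2-T7 | 6% | 1% | 0% |

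The simulated effect sat at T2, T4 and T6. With equal correlations, an effect at T3, T5 and T7 gives the same results. A closed-form check uses a non-central chi-square with noncentrality (n/2) × Σ(dⱼ − d̄)² / [SD²(1 − ρ)]. For D = 0.5 over T1-T7, Σ(dⱼ − d̄)² = 3×0.25 − 7×(1.5/7)² = 0.429. The noncentrality is 5.36, 7.50 and 12.50 on 6 df, giving misses of 64%, 50% and 24%, which agrees adequately.

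**Step 3: power of each analysis at D = 0.75, ρ = 0.5.** For a mean of k visits, SE = √{2 × SD² × [1 + (k − 1)ρ] / (k × n)}, and power ≈ Φ(effect/SE − z).
- Three-visit contrast: SE = √(2×4×2/(3×70)) = 0.276. 0.75/0.276 = 2.717, so power is 78% (z = 1.960), or 68% with alpha halved for two contrasts (z = 2.241).
- T1-T7 main effect, one phase: SE = √(2×4×4/(7×70)) = 0.256. Effect 0.321, power 24%.
- One visit, Bonferroni over seven (z = 2.690): SE = √(2×4/70) = 0.338. Power 32%. At D = 0.5 and 1.0 it is 11% and 61%.
- Effect in both phases, T1-T7 main effect: 0.643/0.256 = 2.515, power 71%.
- Effect in both phases, T2-T7 average: SE = √(2×4×3.5/(6×70)) = 0.258, power 83%.

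The contrast powers make no allowance for any gain from baseline adjustment.

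**The case against.** The strongest reply is that the plan already tests for this. An effect in one phase only is a treatment-by-time interaction, and a significant one leads to comparisons at each visit. This stands in part: a 1.0-point one-phase effect is nearly always caught, and the pooled result is reached only when the interaction is not significant. The remark in 3.6 that visit-level effects go unadjusted in that branch also suggests they would still be visible. But small effects are often missed. When the test is significant, the plan offers single-visit tests of low power rather than an estimate of acute or sustained relief.

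Second, whatever the recall windows are, they are the same in both randomised arms, and differences between visits are absorbed by the time factor. This stands: the question is what is being estimated, not bias between arms.

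Third, a reader might infer that half of the pooled effect rests on about 2% of follow-up. The documents do not support that as a finding. Three half-hour sessions make 1.5 h, which is 2.1% of 72 h, 2.5% of 60 h or 3.1% of 48 h. But this requires the undefined period at T2, T4 and T6 to be exactly the session, and the clock times are not given. Section 3.4 also places the mood scales before the pain re-rating at T2. The weight of the after-session ratings over the listed visits is 3/7, not one half. Nor is a mean over scheduled visits offered as a time-weighted average.

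Fourth, extra contrasts could be left to a statistical analysis plan. The pooling rule, however, is written into 3.6, and the recall window is a data-collection instruction that belongs in 3.4.

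**Conclusion.** The point holds for the two secondary pain scores. When the interaction is not significant, the planned main effect averages two different quantities and a pre-treatment visit. A one-phase effect shrinks to 43% of its size over T1-T7, or to 50% over T2-T7; these fractions need only equal visit weights. The miss rates of the interaction test (roughly 20-65% for 0.5 points; for 1.0 point at most about 4% over T1-T7 and 6% over T2-T7) and the power figures rest on the assumed SD of 2 and equal correlations. That the two sets of ratings cover different windows is inferred from the wording and schedule; that the windows are not stated is plain.

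It would be wrong to conclude that the trial's main result is compromised. The primary outcome is the rate of moderate to severe contraction pain on the third postoperative day, a single time point, and the sample size is set for it. The incidence model would be touched only if its main effect over visits were reported in place of the day-3 comparison. This is a worthwhile, low-cost improvement to secondary analyses.

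**What to change.** In section 3.6, for contraction pain and for incision pain, prespecify two contrasts from the same GEE:
- **Acute effect:** mean group difference over T2, T4 and T6.
- **Sustained effect:** mean group difference over T3, T5 and T7.

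Enter T1 as a baseline covariate rather than an outcome level. Report both contrasts whatever the interaction test shows, in place of the pooled main effect. Label each for what it measures; the sustained contrast should not be renamed as the whole three-day outcome, which 3.5.2 defines over T1-T7. In section 3.4, state the recall window for every pain rating, including what the period at T2, T4 and T6 covers.

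The cost is two secondary estimates per pain score instead of one, which need a multiplicity adjustment or an exploratory label. If the effect is the same in both phases, each contrast has somewhat less power than a T2-T7 average: at 0.75 points and correlation 0.5, 78% (68% with alpha halved) against 83%. No visit is added and the sample size does not change.

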### **3.5 Outcome measures**

#### **3.5.1 Primary outcome**

The primary outcome is the incidence of moderate to severe uterine contraction pain on the third postoperative day. Pain intensity is evaluated using the Visual Analogue Scale (VAS). The VAS is a well-established tool for evaluating pain, consisting of a 100 mm line where one end represents "no pain" and the other end signifies "the worst pain imaginable" or "the most extreme pain possible". Participants are asked to mark the point on the line that best corresponded to their perceived pain intensity. In this study, uterine contraction pain is classified as moderate to severe if the VAS score is 4 or higher.

#### **3.5.2 Secondary outcomes**

1) Peak uterine contraction pain scores during the three days postoperatively (assessed by the VAS). The contraction pain scores are measured before the

first intervention (T1), after the first intervention (T2), before the second intervention (T3), after the second intervention (T4), before the third intervention (T5), after the third intervention (T6), and the third postoperative day (T7).

2) Incision pain scores at T1-T7 (assessed by the VAS).

3) Maternal anxiety scores at T2, T4, T6, T7 and the first month postpartum [T8] (assessed by the Pregnancy-Related Anxiety Questionnaire-Revised 2 [PRAQ-R2], comprising 10 items, each rated on a 5-point scale [1-5], with higher scores indicative of increased pregnancy-related anxiety).

4) Maternal depression scores at T2, T4, T6, T7, and T8 (assessed by the Edinburgh Postnatal Depression Scale [EPDS], including 10 items, scored on a 4-point scale [0-3], with higher scores denote more severe depressive symptoms).

5) Sleep quality at T2, T4 and T6 (assessed by the Leeds Sleep Evaluation Questionnaire [LSEQ], with higher scores indicating better sleep quality).

6) Quality of postpartum recovery at T4, T6 and T7 (assessed by the 11-item Obstetric Quality Recovery Scale [ObsQoR-11], with a total score range of 0-110).

### **3.5.3 Adverse Events**

Adverse events (AE) refer to unforeseen medical occurrences experienced by clinical study participants. Adverse events are typically mild discomforts, with the most common being ear pain, headache, and tingling sensations. Some

patients may experience mild headaches or localized tingling. In this study, investigators will observe participants' facial expressions and verbal responses when they first receive stimulation, avoiding leading questions (such as inquiring whether the participant experiences tingling or discomfort).

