#### **4. Data and Safety Monitoring**

The clinical study will implement a comprehensive safety monitoring plan based on a thorough risk assessment. Throughout the study, all adverse events (AEs) will be meticulously documented, promptly addressed, and continuously monitored until resolution or stabilization of the patient's condition. Serious adverse events (SAEs) and unexpected incidents will be reported immediately to the ethics committee, regulatory authorities, and drug oversight agencies as required by the protocol. The principal investigator will conduct periodic comprehensive reviews of all AEs and, if necessary, convene an investigator's meeting to evaluate the risks and benefits associated with the study. This trial is designed as a double-blind study, and blinding will be broken only when necessary to ensure participant safety and rights. Independent data monitoring personnel will be assigned to continuously oversee the study data. For high-risk studies, an independent Data Safety Monitoring Board (DSMB) will be established to review accumulated safety and efficacy data and determine whether the study should proceed.

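### Section 3.5.3 defines adverse events as unforeseen although it lists expected ones, gives a detection method confined to the start of stimulation, and counts tingling that titration provokes in both arms

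*Protocol*

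**What the plan says.** Three sections of the protocol bear on how harms are found, and a fourth sets the visit schedule.

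- **Section 3.5.3, definition.** "Adverse events (AE) refer to unforeseen medical occurrences experienced by clinical study participants". The next sentence describes these events as usually mild, "with the most common being ear pain, headache, and tingling sensations".
- **Section 3.5.3, method.** Investigators are to watch participants' "facial expressions and verbal responses when they first receive stimulation, avoiding leading questions". Asking whether the woman feels tingling or discomfort is the example of a question to avoid.
- **Section 3.8, active arm.** Each session starts "with the current increasing for 30 seconds until the participant reports a tingling sensation"; the current is then set slightly below that level and runs for 30 minutes.
- **Section 3.8, sham arm.** The start is the same, "with the current increasing for 30 seconds until the participant reported a tingling sensation", with the same step down, "after which the device remained off for the following 30 minutes to simulate the sham state".
- **Section 3.8, monitoring.** "Throughout the intervention, researchers closely monitor participants for any adverse effects", and stimulation stops if effects are intolerable.
- **Section 4.** Over the whole study, "all adverse events (AEs) will be meticulously documented" and followed until they resolve or stabilise.
- **Section 3.4.** The visits T0 to T8 are listed with their assessments: baseline data, pain, sleep, depression, anxiety and recovery quality. No visit includes an inquiry about adverse events.

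**The concern.** The definition and the method of collecting adverse events belong in the protocol, because they govern what ward staff write down. Here the definition conflicts with the examples that follow it. The only described way of finding events is placed where the two arms receive the same thing. One of the three named events is also a step in the procedure itself.

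At stake is the tolerability comparison. Section 2 motivates taVNS partly by the side effects of existing analgesics, so readers will look to this trial for credible data on its own side effects. If mild events are recorded according to each investigator's reading of 3.5.3, or only when a woman happens to mention them, the counts will be incomplete and hard to interpret. This applies most to ear pain and headache that begin during the 30 minutes of stimulation or later.

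**Working it through.** Section 3.5.3 contains no figure to reproduce. The only number used below is the planned 78 per group in Section 3.7, which does reproduce:

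- n = (1.960 + 0.842)² × (0.35 × 0.65 + 0.15 × 0.85) / 0.20² = 69.66, rounded up to 70 per group.
- 70 / 0.90 = 77.8, rounded up to 78 per group.

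The rest is a comparison of the sections.

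**1. Definition against examples.** Section 3.5.3 restricts adverse events to what was not foreseen, then names three that are foreseen. Applied literally, the first sentence excludes all three events named in the second. Section 4 has no definition of its own, so its promise to document every adverse event relies on the one in 3.5.3.

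**2. Method against treatment contrast.** From Section 3.8:

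| Phase of session | Active | Sham |
|---|---|---|
| 30-second rise to reported tingling | yes | yes |
| Step down to just below that level | yes | yes |
| Next 30 minutes | stimulation on | device off |

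The method in 3.5.3 applies when stimulation is first received. This could mean the first session or the start of each session. On either reading it falls in the first rows, where the arms do not differ. Observation at that moment cannot by itself separate active from sham.

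**3. What the other sections add.** Section 3.8 covers the third row, because it has researchers monitor throughout the intervention. Section 4 covers the time between and after sessions. Both state that monitoring takes place; neither says how an event is elicited. Section 3.4 sees every woman at T2, T4, T6 and T7 but schedules no question. An event mild enough not to show, or one that starts after the researcher has left, reaches the record only if someone notices it or the woman volunteers it.

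Suppose the true difference in event risk between the arms is d and a share c of events is captured, the same in both arms. The expected observed difference is then c × d. It is diluted when c is below 1, and it is not zero unless c or d is zero. The documents give neither c nor d, so no numerical loss can be stated.

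**4. Tingling.** Under 3.8 the current rises until the woman reports tingling, at each session and in both arms. Assume every woman reaches that point.

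- If titration tingling counts as an adverse event, the result is 78 of 78 against 78 of 78, a difference of 0.
- If it does not count, the ramp contributes 0 in both arms. Only tingling after the ramp could then differ, and 3.5.3 does not mark it off.

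The text does not say which applies, so staff could follow either reading or mix them.

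**The case against.** The strongest reply is that Section 3.5.3 should not be read alone. It does not say that observation at first stimulation is the only method. Section 3.8 has researchers watch for any adverse effect throughout the session, which includes the 30 minutes when one device is on and the other off. Section 4 extends documentation to the whole study. This stands, and it limits the point. A reader might infer that events are looked for only at first stimulation, that the trial therefore cannot show harm, or that a finding of safety is built in. The documents support none of these: monitoring is stated to cover the period in which the arms differ.

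A second reply is that no investigator would exclude the very events that the section names, and that Section 4 mentions unexpected incidents separately from adverse events, which suggests the broader meaning was intended. That is probably right about the intention. It shows that the wording needs correcting, and the correction is easy.

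A third reply is that avoiding leading questions is sound in a sham-controlled trial that depends on participants' blinding. Agreed. The text rules out leading questions, not neutral ones, so an open question put identically to both arms is compatible with it.

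Last, the trial's stated objective is efficacy, no safety hypothesis is given, and analysis details for adverse events may sit in a statistical analysis plan that is not shown. The absence of an adverse-event analysis is therefore not part of this point. The definition and the detection method are stated in the protocol, and they are what needs correcting.

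**Conclusion.** The point holds as an inconsistency in stated text together with a weak method of finding events. Section 3.5.3 conflicts with its own examples, describes detection more narrowly than Sections 3.8 and 4, and lists as an adverse event the sensation used to set the current. With no inquiry scheduled in 3.4, mild or delayed ear pain and headache are likely to be under-recorded, and the tingling count says nothing about active against sham.

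The consequence is an incomplete and possibly diluted tolerability comparison. Its size cannot be given, because the documents contain no event rates or capture rates. The conclusion rests on two readings: that first receiving stimulation means the titration phase described in 3.8, and that women generally reach the tingling end point. The primary outcome and the sample size are unaffected. The change should be made because it is cheap and improves the method as stated.

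**What to change.** Reconcile Section 3.5.3 with Sections 3.8 and 4, as follows.

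- **Definition.** An adverse event is any untoward medical occurrence from the first session to T7, whether expected or not.
- **Tingling.** Tingling reported during the titration ramp is part of the procedure and is not an adverse event. Tingling or ear pain that starts or persists after the ramp is.
- **Elicitation.** At T2, T4, T6 and T7, ask one neutral open question in the same words in both arms, for example whether the woman has noticed anything unusual since the last visit. Record the event, its onset and the session it relates to. Add this to Section 3.4.
- **Reporting.** Give the number of women with at least one event per arm.

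The cost is a change of protocol wording and one question at four assessments that already take place. The small downside is that more minor events will be recorded in both arms.
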